## Abstract

**Background:**

Prevalence estimates for insomnia range from 10 to 50% in the adult general population. Sleep disturbances cause great impairment in quality of life, which might even rival or exceed the impairment in other chronic medical disorders. The economic implications and use of health-care services related to chronic insomnia represent a clinical concern as well as a pronounced public health problem. Hypnotics are frequently prescribed for insomnia, but alcohol and over-the-counter sleep aids seem to be more widely used by insomniacs than prescription medications. Despite the complex relationship between insomnia and physical and mental health factors, the condition appears to be underrecognized and undertreated by health care providers, probably due to the generally limited knowledge of the causes and natural development of insomnia.

**Methods/Design:**

The Tromsø Study is an ongoing population-based cohort study with five previous health studies undertaken between 1974 and 2001. This protocol outlines a planned study within the sixth Tromsø Study (Tromsø VI), aiming at; 1) describing sleep patterns in a community-based sample representative of the general population of northern Norway, and 2) examining outcome variables of sleep disturbances against possible explanatory and confounding variables, both within a cross-sectional approach, as well as retrospectively in a longitudinal study – exploring sleep patterns in subjects who have attended two or more of the previous Tromsø studies between 1974 and 2009. First, we plan to perform a simple screening in order to identify those participants with probable sleep disturbances, and secondly to investigate these sleep disturbances further, using an extensive sleep-questionnaire. We will also collect biological explanatory variables, i.e. blood samples, weight, height and blood pressure. We plan to merge data on an individual level from the Tromsø VI Study with data from the Norwegian Prescription Database (NorPD), which is a national registry including data for all prescription drugs issued at Norwegian pharmacies. Participants with sleep disturbances will be compared with pair-matched controls without sleep disturbances.

**Discussion:**

Despite ongoing research, many challenges remain in the characterization of sleep disturbances and its correlates. Future mapping of the biological dimensions, natural history, as well as the behavioral and drug-related aspects of sleep disturbances in a representative population samples is clearly needed.

## Background

Insomnia is the subjective complaint of insufficient sleep quantity or quality leading to impaired daytime functioning, usually linked to difficulties in falling asleep, trouble staying asleep, waking up too early in the morning or non-restorative sleep [1]. The real prevalence of insomnia is not known, but prevalence estimates, which in part are influenced by diagnostic definitions, range from 10 to 50% in the adult population [2].

Insomnia is classified as transient (no more than a few nights), acute (less than 3 to 4 weeks), and chronic (more than 3 to 4 weeks). Transient or acute insomnia usually occurs in people with no history of sleep disturbances and is often related to an identifiable cause [3]. Chronic insomnia is further divided into primary and secondary conditions, depending on the cause [4]. When the complaint of insomnia is not caused by other medical, psychiatric or medication-related disorders, it is considered to be primary in nature [4]. It is estimated that primary insomnia accounts for approximately 25% of all chronic insomnia [5]. Recently, The American National Institutes of Health State-of-the-Science Conference suggested that insomnia should be conceptualized as a disorder in and of itself, which is or is not comorbid with other disorders – rather than drawing conclusions about insomnia's primary or secondary status [6].

Excessive daytime sleepiness is a key symptom of any type of disturbed sleep. Sleepiness is defined by recurrent episodes of drowsiness or involuntary dozing that arise mainly in sedentary situations. Sleepiness should not be confused with fatigue or tiredness. Although subjective reports of sleepiness are common in people with insomnia, many studies report normal or even heightened levels of daytime alertness among insomniacs, e.g. as measured with the Epworth sleepiness scale (ESS) [7,8] or the Multiple Sleep Latency Test (MSLT) [9-12]. On the other hand, insomnia patients usually experience more fatigue than patients with other sleep disturbances, such as obstructive sleep apnea, narcolepsy or periodic limb movements during sleep [7,13].

A wide range of factors are associated with chronic insomnia (Table 1). Precipitants of acute insomnia may include acute medical illness, hospitalization, changes in the sleeping environment, medications, jet lag, and acute or recurring psychosocial stressors [3]. Chronic insomnia is often linked to or associated with various underlying medical, behavioral, and environmental conditions [3,14,15], and various medications [14-16]. Especially mental disorders and discomfort are frequently reported by insomniacs. In a survey of 811 respondents, 40% of those with insomnia (compared with 16% of those without), met the criteria for one or more psychiatric diagnoses [17]. Although it is difficult to discern whether a psychiatric disorder precipitates insomnia or whether insomnia makes an individual vulnerable to the emergence of a psychiatric disorder, investigations indicate an increased risk for new onset of depression, anxiety disorders, and substance abuse in people with persistent insomnia [18]. Additionally, insomnia may be precipitated by factors like stress and perpetuated by behavioral factors, or unstable sleep schedules. Shift work or other lifestyle factors that disrupt circadian rhythm increase the risk of sleep disturbances [19].

**Table 1 T1:** Factors related to chronic insomnia

Specific sleep disturbances:
• Circadian rhythm disorders:
◦ Advanced sleep-phase syndrome
◦ Delayed sleep-phase syndrome
• Sleep apnea (obstructive, central, or mixed)
• Restless leg syndrome
• Periodic limb movement disorders (nocturnal myoclonus)
• Parasomnias, i.e. REM-sleep-behavior-disorder
Physical illness:
• Pain: arthritis, musculoskeletal pain, other painful conditions
• Cardiovascular: heart failure, nocturnal breathlessness, nocturnal angina
• Pulmonary: chronic obstructive pulmonary disease, allergic rhinitis (nasal obstruction)
• Gastrointestinal: gastroesophageal reflux disease, peptic ulcer disease, constipation, diarrhea, pruritus ani
• Urinary: nocturia, incomplete bladder emptying, incontinence
• Central nervous system: stroke, Parkinson disease, Alzheimer disease, seizure disorder
• Psychiatric illness: anxiety, depression, psychosis, dementia, delirium
• Pruritus
• Menopause (hot flushes)
Behavioral: daytime nap, early retirement to bed, use of bed for other activities (eg, reading and watching television), heavy meals, lack of exercise, and sedentary lifestyle
Environmental: noise, light and other disturbances, extreme temperatures, uncomfortable bedding, and lack of exposure to sunlight
Medications:
• Central nervous system stimulants: sympathomimetics, caffeine, nicotine, amphetamines, ephedrine, phenytoin
• Antidepressants: bupropion, selective serotonin reuptake inhibitors, venlafaxine
• Anti-Parkinsonian agents: levodopa
• Bronchodilators: theophylline
• Cardiovascular: B-blockers, diuretics
• Histamines, H_2 _blockers: cimetidine
• Anticholinergics
• Corticosteroids
• Alcohol
• Herbal remedies
• Stimulant laxative

REM = rapid eye movement.

An association between elevated body mass index (BMI) and short sleep duration has been demonstrated in recent years [20]. A possible causality between short sleep duration and the development of diabetes mellitus (DM) has also been explored. Gottlieb et al. [21] reported that short sleep duration is associated with DM and impaired glucose tolerance (IGT) in community-dwelling middle-aged and older adults. This association persisted after adjustment for known DM risk factors. Sleep restriction to four hours of sleep per night increased blood pressure, decreased parasympathetic tone, increased evening cortisol and insulin levels, and promoted increased appetite, possibly through the elevation of ghrelin, a pro-appetitive hormone, and decrease in levels of leptin [22-24]. The correlation between short sleep duration with DM and IGT may partly explain the association between short sleep duration and coronary heart disease [25] and all over mortality [26-28].

Sleep patterns change throughout life. It seems as if ageing makes it more difficult to stay asleep at night and to stay awake during the day [29]. Total sleep time during the 24-hour period appears to decline with advancing age, accompanied by a redistribution of sleep – with decreased nocturnal sleep and increased daytime napping [29]. Progressive physical inactivity, dissatisfaction with social life, and presence of physical and mental problems may be the most predictive factors of insomnia in the elderly [30]. Opposed to healthy elderly, sleep duration during the 24-h day in demented nursing home patients seems to increase according to the degree of dementia [31]. Some researchers claim that ageing probably is the single most important factor that determines human sleep – more so than gender and even most physical and mental illnesses [32]. However, challenging findings of *no *reduction of nocturnal sleep with age in healthy elderly have also been presented, suggesting that insomnia in the elderly is not related to ageing itself [33-35].

It is known that hypnotics are frequently prescribed for insomnia [36]. However, alcohol and over-the-counter (OTC) medications seem to be more widely used by insomniacs than prescription medications [37], perhaps due to the fact that most insomniacs do not discuss their sleep problems with their doctor [38]. In a general population sample of 2.181 adults aged 18 to 45 years, Johnson et al. [37] found that 25.9% had used any substance as a sleep aid in the past 12 months. Approximately 18% reported using medications (57% of these being OTC-drugs), and 13% reported using alcohol to fall asleep. The choice of substance used as a sleep aid seems to be affected by sociodemographic characteristics: Most chronic benzodiazepine users tend to be elderly [39], and more men than women use alcohol to induce sleep. Rokstad et al. [40] examined the prescribing patterns among general practitioners (GPs) in a Norwegian county in relation to the patients' age, gender and the diagnosis for prescribing, and found that insomnia was among the most commonly recorded diagnosis for prescribing. Most drugs have not been sufficiently studied to determine their primary effects on sleep and waking behavior [41]. Even when the effects of a drug are known, the medication may act differently in normal individuals and individuals who are ill [41].

The economic implications and use of health-care services related to chronic insomnia represent a major problem. Costs related to chronic insomnia do not only include the direct costs of health-care, but also the indirect costs related to absence from work, diminished productivity, accidents, and other health problems that are, at least in part, secondary to insomnia [42-44].

Compared to other sleep disturbances, such as narcolepsy and sleep apnea, the understanding of the basic pathophysiology of insomnia has lagged behind [45]. This discrepancy probably stems from the heterogeneous nature of insomnia. On one hand, insomnia may be a primary condition with a pathophysiology, like a general state of hyperarousal – which includes changes like increased levels of catecholamines [46], increased basal metabolic rate [47], increased body temperature [48], altered heart rate [47], increased level of central nervous system (CNS) metabolic rate [49], and elevated electroencephalograph activity [50,51]. On the other hand, insomnia may be a co-existing condition with numerous physical and mental disorders.

Further knowledge of the impact of latitude, daytime illumination and season, on the prevalence of insomnia is needed [52]. The term "midwinter insomnia" has been applied for the seasonal type of insomnia observed in arctic areas during the dark periods of the year [53], but the possible consequences of annual variations in environmental light on sleep are still not settled [52,54], and make arctic sleep studies especially relevant.

Semantic as well as definition confusions are present in many epidemiological sleep studies. This situation probably rises from the fact that no single and clear definition exists of insomnia and how to assess it [33]. As a result, very different and non-comparable sleep assessment tools exist – making it is almost impossible to compare and summarize studies.

Our knowledge of insomnia is still limited, especially regarding its evolution and consequences in the general population [33]. Future sleep research is in need of validated measurements of sleep complaints, in order to provide common metrics for describing insomnia and insomniacs in epidemiological studies.

Below, we describe the protocol for a longitudinally, retrospective cohort survey and a cross-sectional study in a large representative adult community sample in northern Norway (The Tromsø Study). Using validated sleep assessment tools, our aim is to describe and analyze sleep disturbances, with their correlating and predisposing factors.

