## Methods

### Setting

The current study will be performed in a non-institutionalized general population in northern Norway, aged 20 to 90 years. Samples will be drawn in a two-stage procedure, described below.

In the first stage, data from all eligible participants in the Tromsø VI Study will be assessed, in order to describe sleep disturbances and their associated risk factors. In the initial survey, self-reported sleep disturbances will be addressed in questionnaire 1 (Q1), with one single question; "During the last 12 months, how often have you experienced sleep disturbances?", answered with a four-item response: *"never", "1–3 times per month", "once a week" *or *"more than once a week"*. In this initial screening, the selection criterion for sleep disturbances will be *"more than once a week"*.

In the second stage, all participants who report sleep disturbances ("*more than once a week"*) will be invited to a second cross-sectional survey, where sleep complaints and daytime sleepiness will be mapped, using a sleep assessment questionnaire (questionnaire 2 = Q2) described below. A pair-matched control group (matched for age and gender) will be recruited among the remaining participants (those without sleep complaints).

Assuming that the prevalence of sleep complaints in the Tromsø VI Study corresponds to previous estimates for the general population, we expect to include 10 to 15% of the total study population into the sleep complaint group.

In order to analyze possible seasonal effects due to the natural annual light-dark cycle in the artic, we will examine a random half of the participants in the sleep complaint group and control group with Q2 in the part of the year with the highest levels of environmental light (May-June), and examine the remaining participants with Q2 in the part of the year with the lowest levels of environmental light (November-December).

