### Outcome measures

Outcome measures in the first part of this study will be the prevalence of sleep disturbances as reported in the initial questionnaire (Q1) containing a four-item response option, where sleep disturbance is defined as the average occurrence of sleep problems *"more than once a week"*.

In the second part of the study, sleep characteristics will be further mapped by a sleep questionnaire (Q2), sent by mail to subjects in the sleep complaint group and in an approximately equal-sized control group. Recruitment, pair matching, questionnaire logistics (including reminders) will be handled by the Tromsø Study's central body, situated at the University of Tromsø. Outcome measures are summarized in Table 3.

**Table 3 T3:** Sleep outcome variables, potential explanatory variables and their pre-specified associations in the Tromsø Study

*Sleep outcome variables against potential explanatory variables*	*Pre-specified associations*	*References*
Initial screening of all eligible participants in the Tromsø Study:		
• Prevalence of sleep disturbances reported in the initial questionnaire (Questionnaire 1) containing a four-item response option, where sleep disturbance is defined as the average occurrence of sleep problems *"more than once a week"*.	10 to 50% in the adult population.	[2, 76]
• Sleep disturbances and their possible relationships, including demographic variables, health-related variables, and lifestyle and socioeconomic variables, and biological markers.	Increased risk for impairments in health, decreased quality of life and increased healthcare utilization.	[19, 65, 77-80]

Further mapping with validated sleep assessment questionnaires among subjects with sleep complaints selected in the initial screening and their control group:		
• Sleep outcome variables related to the use (dose and frequency) of specific prescription drugs, derived from the Norwegian Prescription Database (NorPD).	Frequent use of hypnotics and over-the-counter (OTC) medications.	[36, 37]
• Sleep outcome variables related to socioeconomic variables.	Insomnia related to unemployment and socioeconomic deprivation, more common in women, elderly and individuals living alone.	[81, 82]
• Sleep outcome variables and excessive daytime sleepiness related to objective medical diagnosis, such as diabetes and coronary disease.	A possible link between short sleep, diabetes mellitus, coronary heart disease and all over mortality.	[21, 25-28]

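### A 12-month average case definition can class moderate or short winter-only insomnia as a non-case, and the later exclusion of changed-status subjects can then weaken the planned light-dark comparison

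*Protocol article*

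**What the plan says.** The Background names midwinter insomnia, a term that "has been applied for the seasonal type of insomnia observed in arctic areas during the dark periods of the year". It calls for more knowledge of how season affects the prevalence of insomnia.

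Setting then lays out the screening and the seasonal comparison:

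- **Screening.** One item in the first questionnaire (Q1) asks "During the last 12 months, how often have you experienced sleep disturbances". There are four answer options, and only the top one, *more than once a week*, makes a case. The item does not ask about season.
- **Controls.** A group matched on age and gender "will be recruited among the remaining participants (those without sleep complaints").
- **Season.** "In order to analyze possible seasonal effects due to the natural annual light-dark cycle in the artic", the plan will "examine a random half of the participants in the sleep complaint group and control group with Q2" (the sleep questionnaire) in May-June, and the rest in November-December.

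Under Outcome measures, "sleep disturbance is defined as the average occurrence of sleep problems" more than once a week. The same item supplies the first outcome: "Outcome measures in the first part of this study will be the prevalence of sleep disturbances as reported in the initial questionnaire (Q1").

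The Statistics section adds that cases who reach normal values by the time of Q2, and controls who move the other way, are excluded from later analyses together with their matched partner.

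**The concern.** The seasonal comparison is run in groups formed by an item that averages over the year. A person who sleeps badly for part of the winter and well otherwise can fall under the threshold and so be placed among the non-cases. If that person becomes a control, dark-season Q2 data should reveal the problem, but the exclusion rule then removes exactly the people in whom it was revealed.

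Two things are at stake. A small or absent light-dark difference could be produced partly by selection and exclusion. And the first-part prevalence, being a 12-month figure, cannot say how common insomnia is in the dark months, which is the gap the Background describes.

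**Working it through.** **Inputs from the protocol.** 12-month look-back (Setting). Case threshold: an average above once a week (Outcome measures). Seasonal windows May-June and November-December (Setting). Exclusion of changed-status subjects with their partners (Statistics).

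**Inputs assumed.** The protocol gives neither the length of a midwinter episode nor the nights affected per week. I take 2 to 6 months and 3 to 7 nights a week, with no bad nights outside the episode.

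**The plan's own figures.** The stated pair numbers reproduce with n = (SD × (1.960 + 1.282) / difference)², rounded up:

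- PSQI: (4.58 × 3.242 / 2)² gives 56.
- ESS: (5.9 × 3.242 / 2)² gives 92.
- BMI: (5.7 × 3.242 / 1)² gives 342.

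All three are sized for case-control differences. None is sized for a seasonal contrast.

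**Who passes the threshold.** 12-month average = nights per week in the episode × weeks of episode / 52. To exceed 1, the nights per week must exceed 52 / weeks.

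| Episode | Weeks | Nights a week must exceed | Average at 3 a week | Average at 5 a week | Average at 7 a week |
|---|---|---|---|---|---|
| 2 months | 8.7 | 5.98 | 0.50 | 0.84 | 1.17 |
| 3 months | 13 | 4.00 | 0.75 | 1.25 | 1.75 |
| 4 months | 17.3 | 3.01 | 1.00 | 1.66 | 2.33 |
| 6 months | 26 | 2.00 | 1.50 | 2.50 | 3.50 |

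Five bad nights a week through November and December averages 0.84, a non-case. Three a week for three months averages 0.75, also a non-case. Seven a week for two months averages 1.17, a case.

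**Where the non-cases go.** The remaining participants include everyone who answered *1-3 times per month* or *once a week*. People without sleep complaints, read literally, do not. The control sentence uses both descriptions as if they were the same. On the first, a winter-only sufferer below the threshold is eligible as a control. On the second, that person is neither case nor control and is absent from Q2.

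**What the exclusion does.** Take two controls with the same winter-only insomnia, randomised to different halves, and assume Q2 reflects current sleep.

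- Surveyed in November-December: abnormal, status changed, dropped with the matched case.
- Surveyed in May-June: normal, kept.

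Among cases the rule acts in the same direction. A severe winter-only case surveyed in May-June may have normalised and is dropped; surveyed in November-December, the same person is kept. On whichever Q2 measure defines normal (the protocol does not say), the controls kept are normal in both seasons and the cases kept are abnormal in both. A contrast in that binary status disappears by construction, and a contrast in the continuous score is truncated.

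**Prevalence.** The first-part outcome is the same 12-month item, so it yields one figure that does not separate dark from light months.

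**The case against.** The other side has real strength.

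- **Severe winter insomnia does qualify.** A reader might infer that everyone with midwinter insomnia is a non-case and that seasonal insomnia has been largely removed from the case group. The table shows otherwise, and the protocol gives no episode length or frequency from which to say what share is lost.
- **Respondents are not asked for an average.** That word appears in the outcome definition, not in the item. Someone with a bad winter may answer for it and be classed as a case. This stands, and it leaves classification depending on how the item is read.
- **The control wording may bar these people.** So it does on one reading. The two descriptions still conflict, and on the strict one these people are missing from Q2 altogether.
- **Season is studied through Q2, not through Q1 prevalence.** Correct. A reader might infer that winter insomnia stays hidden among controls; the random halves would in fact expose it. What undoes this is the exclusion rule, so the concern about controls depends on that rule.
- **Season is not a main aim.** Neither numbered aim is seasonal, nor is any association in Table 3. A season-neutral entry item also keeps case status from depending on the survey date, which is defensible. This argues for keeping the 12-month definition as the main one. It does not rescue a planned comparison that discards its own signal.

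**Conclusion.** The concern holds in a limited form. Taken as an average, the case definition can place winter-only insomnia of up to about 6 bad nights a week over November-December, or up to 4 a week over 13 weeks, among the non-cases. The control wording does not settle whether such people can be controls. The exclusion rule then removes status changes that differ by season, so the light-dark comparison can understate a seasonal effect. The first-part prevalence is not season-specific.

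This rests on the assumed episode lengths and frequencies, on respondents answering roughly as an average, and on the exclusion applying to the seasonal analysis, which the reference to later analyses suggests but does not spell out.

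The size of the understatement cannot be derived. A reader might try dark-season prevalence = 0.125 + 0.875 × s, with s the share of non-cases affected in winter; s of 5% to 20% gives 16.9% to 30.0% against 12.5%. The documents do not support those figures: s is assumed, and the formula takes every 12-month case to be affected in the dark season.

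**What to change.** Keep the stated 12-month case definition and prevalence outcome as the main ones. Then:

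1. Add one line to the Q1 sleep item: is the trouble mainly in the dark period, mainly in the light period or at no particular time, and how often in that period?
2. Flag as seasonal complainers those above *more than once a week* in that period. Those who already meet the 12-month definition stay cases and carry the flag.
3. Reconcile the two descriptions of the controls, so that flagged people are not eligible.
4. Report the prevalence of seasonal complaints separately.
5. Send flagged people Q2 under the same random halving, and analyse May-June versus November-December with them as a separate stratum.
6. Do not apply the changed-status exclusion in the seasonal analysis.

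The cost is one questionnaire line and some extra Q2 mailings, or fewer year-round cases if mailing is capped. The plan expects 10 to 15% of about 12,000 attenders in the complaint group, that is 1,200 to 1,800. The largest stated need, 342 pairs, was set for the case-control BMI difference, so it does not show adequate power for the seasonal contrast. The flagged stratum is selected by self-reported seasonality, so a light-dark difference within it is to be expected and should be presented as descriptive.
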